## OUTCOME MEASURES AND HYPOTHESES

3

Participant outcome measures were as follows: (a) pain‐related knowledge [primary], (b) pain assessment and management perceptions [secondary], (c) participants’ training endorsements [secondary], and (d) use of evidence‐based pain assessment and management strategies [tertiary]. Between‐group hypotheses predicted that immediately post and at 4‐ to 6‐week follow‐up, participants receiving the pain training would demonstrate significantly higher pain knowledge and pain assessment and management perceptions compared with the control group. It was also predicted that at follow‐up participants receiving the pain training would have significantly higher levels of evidence‐based pain assessment and management strategy use compared with the control group. Within‐group hypotheses for those receiving the pain training predicted significant increases on pain knowledge and pain assessment and management perceptions from pre to post, with maintenance of these gains from post to follow‐up. It was also hypothesized that participants would provide favorable endorsements of the training program. Finally, significant increases from pre to follow‐up for evidence‐based pain assessment and management strategy use were hypothesized. Results from the RCT are to be published in two separate manuscripts: one reviewing the impact of the training on participant knowledge and perceptions, and the other reviewing participants’ training endorsements and its impact on their strategy use in the workplace.

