### Sample size

4.5

G*Power 3^15^ was used to conduct a power analysis based on our previous *Let's Talk About Pain* training pilot study.^13^ Based on the smallest effect size (*d* = 0.90 [effect size *f* = 0.45]; original range of effect sizes *d* = 0.90‐1.71), a very small sample size (16) was required at power of 0.95 and alpha of 0.05 to detect an overall interaction effect of group by time. A much more conservative effect size (*d* = 0.25 [effect size *f* = 0.1250]) was also used to calculate the most stringent estimate at power of 0.95 and alpha of 0.05, resulting in a total target sample size of approximately 84 participants per group (168 participants total; [15). We aimed for our study sample size to fall in the higher end of this range.

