## ANALYSES

8

Research assistants double enter the data into an SPSS statistical analysis program which is stored on an encrypted, password protected e‐drive. Hard copy data will be stored for seven years after publication of results.

Both intention‐to‐treat (ITT) and per protocol (PP) analysis approaches will be used to analyze the data related to the study's primary and secondary outcomes regarding participants’ pain knowledge and pain assessment and management perceptions; ITT will be primary, and PP will be complementary.^22^, ^23^ After confirming there are no baseline differences between groups, seven 2 × 3 mixed analysis of variances (ANOVA) will be conducted. If statistical assumptions for these analyses are not met, a more conservative approach using bootstrapping will be considered and conducted if the program allows; SPPS has some limitations in this regard.^24^ The dependent variables for the different mixed ANOVAs will be the mean of participants’ pain‐related knowledge (primary outcome measure) and pain assessment and management perception rating scores (secondary outcome measures). In all seven analyses, the within‐subjects factor will be represented by participants’ scores on the related measure across pre, post, and follow‐up time periods, and the between‐subjects factor will be the condition (pain training or control training). In keeping with the study's specific hypotheses, follow‐up analyses using one‐way ANOVAs and paired samples *t* tests will be used as needed to further investigate differences in the dependent variables over time within the pain training group if significant group differences are found.

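### The pain-versus-control hypotheses at post and at follow-up get no direct test, because the only named follow-up tests look over time within the pain arm

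*Protocol article*

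**What the plan says.** Outcome Measures and Hypotheses (section 3) gives the between-group predictions first and ties them to two occasions, immediately after training and at 4 to 6 weeks: "participants receiving the pain training would demonstrate significantly higher pain knowledge and pain assessment and management perceptions compared with the control group". Separate within-group predictions for the pain arm follow: a rise from pre to post, "with maintenance of these gains from post to follow‐up".

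Sample size (section 4.5) bases the number of participants on power "to detect an overall interaction effect of group by time", giving 16 in total at f = 0.45 and 168 (84 per group) at f = 0.125.

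Analyses (section 8) states that "seven 2 × 3 mixed analysis of variances (ANOVA) will be conducted", one for the QUPID-CR knowledge score and six for the perception ratings, with condition as the between-subjects factor and pre, post and follow-up as the within-subjects factor. The only tests named after these are one-way ANOVAs and paired t tests, used as needed "to further investigate differences in the dependent variables over time within the pain training group if significant group differences are found". The section names no comparison of the arms at post or at follow-up, and it does not say which ANOVA term counts as a group difference.

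**The concern.** The predictions that randomization can support are that the arms differ at post and that they differ at follow-up. Followed exactly, section 8 yields a group main effect and a group-by-time interaction, and then takes apart only the change within one arm. Neither omnibus test says at which visit the arms differ. The within-arm tests cannot fill the gap, because the same 39-item questionnaire is given three times and a gain within one arm mixes the effect of training with retest and attention effects.

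Durability is at stake. The Introduction lists a longer-term follow-up among the steps the pilot study pointed to. A significant interaction plus a significant within-arm gain could be reported as a lasting benefit over control without the two arms ever having been compared at 4 to 6 weeks.

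The trigger is a second, conditional concern. If it is the group main effect, it includes the pre-training score, where no difference is expected, and it is not the effect on which the trial was sized.

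**Working it through.** **Inputs from the protocol article:** 84 per group, 168 in total; alpha 0.05; f = 0.45 and 0.125; d = 0.25 and 0.90 (section 4.5); two arms and three measurements (section 8). **Assumed, not stated:** correlation ρ = 0.5 between any two measurements, sphericity, unit standard deviation, no clustering by organization, no loss to follow-up. d = 0.50 is added as an intermediate value.

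**1. The plan's own figures.** For the interaction, λ = f² · N · 3 / (1 − ρ), with 2 and 2(N − 2) degrees of freedom.
- f = 0.45, N = 16: λ = 0.2025 · 16 · 3 / 0.5 = 19.44, power 0.970.
- f = 0.125, N = 168: λ = 0.015625 · 168 · 3 / 0.5 = 15.75, power 0.952.

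Both stated sample sizes are reproduced, so the trial was sized on the interaction.

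**2. What the interaction can distinguish.** Take between-arm differences at pre, post and follow-up, centred on their mean.
- Lasting effect (0, d, d): centred (−2d/3, d/3, d/3), sum of squares 2d²/3.
- Effect gone by follow-up (0, d, 0): centred (−d/3, 2d/3, −d/3), sum of squares 2d²/3.

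Both give λ = 168 · (2d²/3) / 4 / 0.5 = 56d², which is 3.5 at d = 0.25 and 14 at d = 0.50. With 2 and 332 degrees of freedom, power is 0.37 and 0.93. The two patterns have identical power, so a significant result does not favour one over the other.

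These figures do not clash with the 0.952 in step 1. Equating 1008f² (step 1 at N = 168) with 56d² gives f = d/√18, so a difference of 0.25 at both later visits corresponds to f = 0.059, not 0.125.

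**3. The trigger, if it is the group main effect.** Under (0, d, d) the mean difference over three visits is 2d/3, and the variance of a three-score mean is (1 + 2ρ)/3 = 2/3. The standardized effect is (2d/3)/√(2/3) = 0.816d, and the noncentrality is 0.816d · √(84/2).

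**4. A direct contrast at one visit, adjusted for the pre score.** The residual variance is 1 − ρ² = 0.75, so the standardized effect is d/√0.75 = 1.155d, and the noncentrality is 1.155d · √(84/2).

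| d | Main effect, pattern (0, d, d) | Interaction, either pattern | Adjusted contrast at one visit |
|---|---|---|---|
| 0.25 | 0.26 | 0.37 | 0.46 |
| 0.50 | 0.75 | 0.93 | 0.96 |
| 0.90 | 0.997 | >0.999 | >0.999 |

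At alpha 0.025, the first step of a Holm procedure over two visits, the adjusted contrast has power 0.35 at d = 0.25.

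**The case against.** Several points on the other side are fair.

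- **The arms are compared.** The mixed ANOVA contains condition and its interaction with time, so the between-group hypotheses do get an omnibus test. This stands; what is missing is a direct test at each stated visit.
- **The within-arm tests have a purpose.** They answer the within-group hypotheses in section 3, and the article does not rank those below the between-group ones. This stands, and the tests should stay.
- **The trigger may be the interaction.** A reader might infer that it is the group main effect, because condition has just been defined as the between-subjects factor. Section 8 does not say so, and section 4.5 points to the interaction. On that reading the loss of power in step 3 does not arise.
- **Within-arm gains would not stand alone.** A reader might infer that the trial could claim uncontrolled gains with no randomized comparison behind them. The text does not support this, since those tests run only after a significant group result.
- **The one-way ANOVAs may have been meant as between-arm tests at each visit.** That is possible, but the sentence confines them to the pain arm.
- **An article condenses the full plan.** Omitting post hoc detail would be no fault. Here, however, the article states the follow-up tests, their scope and their trigger, and these cover only half of the hypotheses they are said to follow.

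At the pilot's effect sizes (d = 0.90 to 1.71) power is ample for every test, so the case rests on which question is tested more than on power.

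**Conclusion.** The mismatch between sections 3 and 8 is real: the time-specific between-group hypotheses get only omnibus tests. At the planned size the interaction has the same power for a lasting effect as for one that has vanished (0.37 at d = 0.25, 0.93 at d = 0.50), so it cannot answer the follow-up hypothesis. This ambiguity remains however large the effect is.

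The point about the trigger is conditional. If it means the main effect, power falls by 0.11 at d = 0.25 (0.26 against 0.37) and by 0.18 at d = 0.50 (0.75 against 0.93), with negligible loss at d = 0.90. If it means the interaction, nothing is lost.

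The power figures rest on a correlation of 0.5 and on ignoring clustering, although whole organizations were randomized; clustering would lower power for the between-arm comparisons. That the two patterns give equal power depends on equal correlations between visits, but under any correlation a two-degree-of-freedom test does not locate the difference in time.

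**What to change.** - Name the group-by-time interaction, not the group main effect, as the omnibus test.
- For the QUPID-CR, specify two pain-minus-control contrasts, at post and at follow-up, each adjusted for the pre score by ANCOVA or a constrained longitudinal model. Report estimates with 95% confidence intervals, and state a testing order or a multiplicity rule.
- Specify the same contrasts for the six perception ratings.
- Do not make these contrasts conditional on a group main effect.
- Keep the within-arm tests, labelled as supportive for the within-group hypotheses.

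**Cost:** no new data, since the pre score is already collected. The adjusted contrasts do not come out of the planned ANOVA, where pre is a level of the time factor, so each outcome needs a second simple model. Because Trial Status reports that data collection ended in August 2018 with analyses ongoing, the report must say that the contrasts were specified after that date.

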### Randomization

4.3

As organizations agreed to host the program(s) for their RW, the entire organization was randomly assigned to either the control or intervention group. This means that all participating staff from a given organization participated in the same condition. Sequentially numbered, sealed, opaque envelopes (SNOSE) with a 1:1 allocation ratio were created by a research assistant not involved in study recruitment, group allocations, training, or data collection processes. Once assigned, primary investigators were no longer blind to the group allocation.

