Frequency and descriptive analyses will be used to analyze participant open‐ended responses on the *Use of Pain Assessment and Management Strategies* and training evaluation questionnaire. To describe responses to open‐ended questions, coding schemes will be developed from an essentialist/realist perspective using an unconstrained matrix.^25^, ^26^ In this scheme, both inductive (ie, consideration of participant responses) and deductive (ie, consideration of relevant research literature) approaches will be incorporated as relevant. For example, category names and descriptions will reflect what is known from previous literature as relevant, but new categories will also be developed that may not be consistent with the literature should they arise. First, the primary investigator will become familiarized with the data, and initial categories will be generated and grouped into broader categories with definitions.^27^ These schemes will then be reviewed by additional researchers on the team who will: (a) help to ensure that the schemes are representative of the data and (b) further develop category definitions and examples.^27^ Following coding scheme development, two research assistants will be trained on these schemes. Participant responses will then be coded, and inter‐rater reliability for coding will be calculated using Cohen's Kappa. An inductive and essentialist/realist qualitative thematic analysis following the steps outlined by Braun and Clarke^28^ will be used to analyze focus group transcript data. Following familiarization with the data, transcriptions will be uploaded to NVivo12 software where meta‐ and subthemes will be derived, defined, and refined. How often a topic is raised, the length of time it is discussed, existing research literature, and applied researcher experience in the field will all be considered in developing these themes. Analyses will occur at the semantic level. Intervention and control focus groups will be analyzed separately from one another.

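### Open-ended strategy-use answers are coded with a scheme begun by an unblinded investigator, with no listed masking step; kappa cannot show a shared lean between arms

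*Protocol article*

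**What the plan says.** Section 4.3 (Randomization) of the protocol article allocates whole organizations and adds: "Once assigned, primary investigators were no longer blind to the group allocation".

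Section 3 (Outcome measures and hypotheses) makes a directional prediction for the tertiary outcome. At follow-up, "participants receiving the pain training would have significantly higher levels of evidence"-based strategy use than controls. It also predicts a rise from pre to follow-up.

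Section 8 (Analyses) lists the coding of open-ended answers in order:

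1. "First, the primary investigator will become familiarized with the data, and initial categories will be generated and grouped into broader categories with definitions". The approach is partly deductive, using the literature where relevant, and partly inductive: "new categories will also be developed that may not be consistent with the literature should they arise".
2. "These schemes will then be reviewed by additional researchers on the team", who check that the scheme fits the data and refine its definitions.
3. "Following coding scheme development, two research assistants will be trained on these schemes".
4. Answers are coded, and inter-rater "reliability for coding will be calculated using Cohen's Kappa".

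The analysis named for these answers is frequency and descriptive. Masking to arm is not mentioned at any of these steps.

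**The concern.** Section 3 compares arms on whether respite workers use evidence-based strategies. For open-ended answers, that depends on human judgement about what an answer means and which category it belongs to. The person who begins the scheme knows which arm each organization is in, has a stated expectation about the direction of the result, and reads the answers before the categories exist. The assistants are then trained on the result.

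If the definitions, or the coders, treat borderline answers from the pain-training arm more generously, that generosity enters the between-arm difference directly. The check applied after coding is agreement between two coders who share the same training and the same scheme. It measures whether they agree with each other, not whether both are wrong in the same direction in one arm.

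**Working it through.** **Step 1: the stated facts side by side.** Section 4.3 gives knowledge of allocation to the primary investigators. Section 8 gives the opening step of scheme development to the primary investigator, after contact with the data. Because allocation was by organization, an organization label on a response is as informative as an arm label. The article says nothing on whether responses carry such labels at that stage, or on what the reviewing researchers and the two assistants know.

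**Step 2: the input for group size.** The article gives no sample-size figure for strategy use. Its target of 84 per group (section 4.5) is for the group-by-time interaction. That figure reproduces. With f = 0.125, N = 168, three time points, and an assumed correlation of 0.5 and sphericity, the noncentrality is 0.125² × 168 × 3 / (1 − 0.5) = 15.75, with 2 and 332 degrees of freedom, and power is 0.952. It is used below only as a plausible group size.

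**Step 3: can kappa see a shared lean?** All inputs other than 84 per arm are assumptions:

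- true rate p = 40% in both arms, so there is no real effect;
- each coder makes an independent random error with probability e = 4%;
- the shared scheme wrongly credits a fraction s of true non-users, in the pain arm only.

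The rate under the shared scheme is q₁ = p + (1 − p)s in the pain arm and q₀ = p in the control arm. Each coder's observed rate is q(1 − e) + (1 − q)e = 0.92q + 0.04. Observed agreement is (1 − e)² + e² = 0.9216 + 0.0016 = 0.9232, whatever s is. With a the mean observed rate over the two arms, chance agreement is Pe = a² + (1 − a)², and kappa = (0.9232 − Pe)/(1 − Pe).

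For s = 20%:

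- q₁ = 0.40 + 0.60 × 0.20 = 0.52;
- the observed rates are 0.5184 (pain) and 0.4080 (control), a difference of 0.1104;
- a = 0.4632 and Pe = 0.5027, so kappa = 0.4205/0.4973 = 0.846.

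| s | Observed rate, pain | Observed rate, control | Spurious difference (points) | Kappa | Chance of p < 0.05 |
|---|---|---|---|---|---|
| 0% | 0.408 | 0.408 | 0 | 0.841 | 5% |
| 10% | 0.463 | 0.408 | 5.5 | 0.844 | 11% |
| 20% | 0.518 | 0.408 | 11.0 | 0.846 | 30% |
| 30% | 0.574 | 0.408 | 16.6 | 0.846 | 57% |

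With true rates from 30% to 50%, kappa stays between 0.82 and 0.85 throughout, and at s = 30% the spurious difference is 14 to 19 points.

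**Step 4: a hand check on the last column.** With both true rates at 50%, the standard error of the difference is √(2 × 0.25/84) = 0.077. A 5-point shift gives z = 0.65 and rejection in about 10% of trials. A 10-point shift gives z = 1.30 and about 25%.

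The rejection rates ignore correlation within organizations. They also presuppose a two-sided 5% test on the coded answers, which section 8 does not name. They show the direction of the effect and are not error rates of this trial. The kappa column does not depend on any test being run.

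**The case against.** The strongest reply is that much of this rests on silence. The article does not say that coders know the arm, that responses carry labels, or that coding is open. Masking of coders could be described in a coding manual, and the introduction says that further information is available on request. That stands for the coders: a reader might infer that they were unmasked, and the text does not support it. It does not remove the point about the scheme. The investigator's knowledge of allocation and leading role in scheme development are both stated, and the steps are listed in sequence in an article that presents itself as the complete protocol. It remains an inference that individual answers could be traced to an arm when they were read.

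A second reply is that safeguards exist: the literature shapes the categories, and other researchers review them. This also stands, so it would be wrong to call kappa the only quality check. These safeguards lower the risk but do not close it. Literature is used where relevant, new categories may be added from the data, and the masking of the reviewers is not stated.

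A third reply is that little depends on these answers. A reader might take them to be the trial's only measure of practice change. Section 6.3 (Tertiary) does not support that: the questionnaire also has closed questions and a standardized vignette, and there are focus groups. Section 8 moreover describes sorting answers into categories and does not say that each is scored as evidence-based or not, or that the prediction in section 3 is tested on coded answers. This limits the reach of the point. Frequencies by arm would still carry any lean if they are set against that prediction.

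**Conclusion.** The point holds in a limited form. An investigator who knows the allocation begins a partly inductive scheme after reading the data. No listed step masks those who develop the scheme or code with it, and Cohen's kappa would not reveal a lean that both coders share. The coded open-ended part of the tertiary strategy-use comparison is therefore open to ascertainment bias.

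This is a risk, not a demonstrated bias, and the documents give no figure for its size. Under the assumptions above, a spurious difference of 5.5 to 16.6 points goes with a kappa of 0.844 to 0.846, against 0.841 with no lean. It would be too strong to say that the trial's false-positive rate is inflated by a known amount, because only descriptive analysis of these answers is planned. The closed questions need no coding. The primary knowledge score (one point per correct item) and the self-ratings are also unaffected. The point is minor, but worth acting on because section 2 (Trial status) says that analyses are ongoing.

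**What to change.** Before scheme development and coding:

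1. A team member exports the open-ended responses in random order under a neutral ID, with arm, organization and time point removed. Organization must go because it identifies the arm, and time point because a pre-to-follow-up rise is also predicted.
2. The team finalises the scheme on the pooled masked file, including which categories count as evidence-based. If unmasked responses have already been read, that classification is taken from the literature.
3. Both assistants code the masked file.
4. Arm is merged only after the codes are locked.

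The report should state who was masked at each step. If masking was already in place, one sentence saying so settles the point.

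The cost is a few hours of data handling, with no extra staff and no change to the sample size. The drawback is that masking will be partial, since some answers reveal the arm by their content.
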